#### Secondary outcomes

Assessment of secondary outcomes will also commence at baseline T0 (recruitment to the study), following completion of the intervention at 8 weeks (T1) and at 4 weeks post-intervention (T2):

*Psychological functioning*: The Chinese version of the Hospital Anxiety and Depression Scale (HADS) will be used to evaluate psychological functioning (anxiety and depression). The 14-item *HADS* was designed as a tool to screen for anxiety and depressive symptoms in medical settings and has well-demonstrated solid psychometric properties for use in medical settings [41–43] and commonly used in burn care settings to screen anxiety and depression [44].

*Sleep pattern improvement*: The Chinese version of the Pittsburgh Sleep Quality Index (PSQI) will be used to evaluate sleep improvement. It includes 19 items with a total score that ranges from 0 to 21. A higher PSQI score implies poorer quality of sleep [45]. In general, a PSQI score greater than 5 is considered to indicate poor sleep quality [45].

*Pain*: The Chinese version of the Brief Pain Inventory will be used to evaluate pain among participants. It has 15 items, of which 11 items have numeric rating scale, on the experience of pain, the area of severe pain, the presence of pain, minimum and maximum pain on the previous day, current pain level, analgesia and pain relief, and the interference of pain on the patient’s functioning [46].

*Itch*: The Chinese version of a visual analogue scale (VAS) will be used to evaluate this outcome among participants. The VAS has been observed to have an intraclass correlation coefficient of 0.88 [47].

*Physical role functioning*/*performance*: The Chinese version of the Disability of the Arm, Shoulder and Hand Symptom Scale (DASH) will be used to evaluate this outcome [48]. The DASH tool is a 30-item questionnaire that asks the patient to grade symptoms and physical function during the preceding week on a five-point Likert scale. The reliability of the DASH is excellent (intraclass correlation coefficient 0.97 with Cronbach’s alpha of 0.97) [48].

*Scarring*: The Vancouver Scar Scale (VSS) will be used to assess this outcome in the current study. The VSS is a validated subjective tool that assesses vascularity, pigmentation, pliability, and height of scars [49]. The tool remains the main tool used to evaluate scarring in burn care research [49]. The total score ranges from 0 to 13 with lower scores implying improved scars.

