### Eligibility criteria

All burn survivors receiving burn care services at the study site will be screened for eligibility during the study period. Adult burn survivors aged ≥ 18 years with burn size ≥ 10% TBSA as assessed by the burn surgeon/burn care nurse (irrespective of the depth of the burn), absence of a confirmed psychiatry condition, renal failure, or diabetes mellitus and reachable on phone and WeChat will be considered for inclusion. Adult burn survivors who are unable to communicate or are enrolled in another rehabilitation trial will be excluded. Drop out will be ascertained based on participants exiting either the control or intervention before the 12th week with no intention to continue their participation. Participants for the follow-up process evaluation phase will be recruited from both arms of the trial. The intervention will be primarily provided and coordinated by two burn care nurses with referrals to other members of the multi-disciplinary burns team which comprises of burn surgeons, rehabilitation medicine specialist, and social worker/psychologist who are involved in caring for burn patients at the study site. These burn care nurses recruited to deliver the intervention will have at least 4 years working experience in the burn unit at the study site and must complete a mandatory training programme which covers contents of the comprehensive transitional care program for burn patients with theory and practice (18 h in total) and passed a competence test prior to participating in the study. Other nurses working in the same unit provide routine care to all patients and are not involved in the intervention. Since most of the nurses working in the unit are not involved with the intervention cases, the risk of contamination is minimal.

The objectives of the mandatory training programme were to enable the burn care nurses to be able to master the concept of transitional care; assess, manage, and monitor the transitional needs of burn patients using the Omaha System and make referral when applicable and demonstrate burns rehabilitation competencies (comprehensive scar, itch, and pain management; psychosocial care; aromatherapy; exercises and splinting; monitoring nutrition and hydration; and infection prevention). See Table 2 for details regarding the training programme.

**Table 2 Tab2:** Details of training programme for burn care nurses based on the TIDieR checklist

TIDieR checklist					

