### Study outcomes

#### Primary outcome

*Quality of life*: Quality of life which is defined as the adult burn survivors’ perceptions of their health status and well-being is the primary outcome for the trial and will be assessed at baseline (T0), following completion of the intervention at 8 weeks (T1) and at 4 weeks post-intervention (T2). The outcome will be objectively assessed using the Chinese version of the Burn Specific Health Scale-Brief and EQ-5D-5L. The BSHS is an outcome scale designed specifically for burns patients. It comprises of four areas: physical, psychological, social relations, and general health condition that is consistent with the biopsychosocial model. A recent review has suggested that generic scales are more sensitive than the BSHS-B domains from one-month post-burn [37]. Thus, as the study will cover up to 3 months post-discharge, the BSHS-B and EQ-5D will be used to measure quality of life in the study. The BSHS-B comprises of 40 questions, 9 sub-scales, and 3 domains (physical, mental, and social). Internal consistency of the total instrument has been reported to be *α* = 0.94 with test-retest reliability suggesting that the intraclass correlation coefficient (ICC) ranged from 0.81 to 0.96 with a total score of 0.93 [38]. The Chinese version has 38 items with a reported Cronbach alpha 0.97 and split half reliability of 0.98 [39]. The EQ-5D-5L is a generic tool to assess quality of life. The instrument has five dimensions: mobility, self-care, usual activities, pain/discomfort, and anxiety/depression. Each dimension has 5 levels: no problems, slight problems, moderate problems, severe problems, and extreme problems. The EQ-5D-5L is a valid extension of the 3-level system (EQ-5D-3L) which is found to have improved measurement properties, with reduced ceiling effect, strengthened discriminatory power and established convergent and known-groups validity [40].

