## Assignment of interventions

### Sequence generation, randomisation, and allocation

Eligible participants who provide written, informed consent will be randomised on a 1:1 basis to one of two trial arms. Prior blocked randomisation list with 75 sets of numbers will be generated using the Research Randomizer and kept in sealed envelopes. As soon as the consent form is received, the RTM will sequentially open the sealed envelopes containing the paper with the number assignment and unfold it. The number written specifies the group to which the adult burn survivor will be allocated. The allocation sequence will be concealed to RN-1 and the research assistant (RA) to minimise bias in the study.

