## Data collection, management, and analysis

### Data collection methods and management

All outcomes will be assessed at baseline (T0); that is after the patient has been recruited. Following the completion of the intervention, the second phase of data collection (T1) will be undertaken; that is at the 8th week. The third phase of data collection (T2) will be the follow-up phase at 4 weeks post-intervention. Data collection will be in the form of completion of questionnaires. The data collection process will be undertaken by three research assistants who will be blinded to the groups of the participants. The research assistants have completed a 10-h training programme covering the outcome measures to be used. Following the training, they undertook a role play to enable the research team to ascertain the inter-rater reliability/percentage agreement with the following results: Burn Specific Health Scale-B (87.7%), EQ-5D-5L (100%), HADS (92.5%), PSQI (86.7%), DASH (84.4%), VAS (100%), BPI (100%), and VSS (100%). All quantitative data will be entered and stored in SPSS Version 25 (SPSS, an IBM company, Chicago, Illinois, USA). All hard copies of documents relating to the study will be stored under lock and key only accessible to designated research team member.

For the follow-up process evaluation phase (qualitative strand), face to face semi-structured interviews with an interview guide will be utilised to collect data after the intervention period has elapsed. Topics for the interview guide will be based on the process evaluation components as highlighted in Table 1. All interview proceedings will be audiotaped and transcribed verbatim in the Trint Automated Transcription Software. Interview transcripts will be exported to QSR NVivo version 10 will be used to manage the data. All soft files related to the study will be kept in a password protected computer only accessible to the principal investigator and the doctoral student investigator. Paper files will be kept under lock and key. For the quantitative phase, we will review the recruitment, enrolment, and follow-up records.

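### The DASH, an arm, shoulder and hand scale, is the only measure assigned to physical role functioning, although entry sets no condition on burn site

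*Protocol article*

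**What the plan says.** The Objectives section of the protocol article lists physical role functioning/performance among the outcomes and does not limit it to a body region. Under Secondary outcomes one instrument is assigned to it: "The Chinese version of the Disability of the Arm, Shoulder and Hand Symptom Scale (DASH) will be used to evaluate this outcome". The description continues: "The DASH tool is a 30-item questionnaire that asks the patient to grade symptoms and physical function during the preceding week". The support offered is reliability (intraclass correlation and Cronbach's alpha, both 0.97). No reason is given for choosing an upper-limb scale.

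Eligibility criteria admits "Adult burn survivors aged ≥ 18 years with burn size ≥ 10% TBSA", whatever the depth. Some medical and practical conditions follow, but none on burn site. Under Data collection methods and management, "All outcomes will be assessed at baseline (T0); that is after the patient has been recruited". No subset is named for the DASH.

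The Primary outcome section already brings in broader measures at the same three times. The BSHS-B is described as having "9 sub-scales, and 3 domains (physical, mental, and social"), and the EQ-5D-5L dimensions include mobility, self-care and usual activities. These serve quality of life. They are not assigned to the physical-functioning objective.

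**The concern.** Reliability shows that a scale gives repeatable scores. It does not show that an arm, shoulder and hand scale covers physical functioning in general. A patient burned on the legs or trunk may be limited in walking or standing, and the DASH, going by its name, is not aimed at that. The programme is not confined to the arm either: the Intervention section offers range-of-motion work, physical therapy and help with daily activities according to need.

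Two things are at stake:

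- **Meaning.** A DASH result, positive or null, would be reported under a broader label than the scale supports. This holds whatever the mix of burn sites, unless everyone has upper-limb involvement.
- **Sensitivity.** Participants with little upper-limb impairment have little room to improve, which pulls the average difference towards zero. A null DASH result could then be read as no effect on physical functioning.

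**Working it through.** **The plan's own figure.** There is none for the DASH. The 38 per arm under Sampling and sample size estimation is for the Burn Specific Health Scale, so nothing in that calculation bears on this point.

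**Comparison of sections.** Objectives: general physical role functioning. Secondary outcomes: a regional scale. Eligibility criteria: any burn site. Data collection: all recruited patients. The mismatch follows from these four statements and needs no arithmetic.

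**Size of the attenuation.** Every input here is an assumption, because the documents give neither the share with upper-limb burns nor any DASH means or SDs.

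- p = share of participants who can respond on the DASH; 0.9, 0.6 and 0.4 are shown.
- d = 0.5 = effect in those participants, in units of their SD, s.
- The remaining participants have zero effect. This is the worst case: any response among them reduces the loss.

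Step 1, average effect: p × d, in units of s. This gives 0.9 × 0.5 = 0.45, 0.6 × 0.5 = 0.30 and 0.4 × 0.5 = 0.20.

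Step 2, information relative to a trial in which everyone can respond: (p × d)² / V, divided by d² / s², where V is the within-arm variance. V depends on how the other participants score.

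- *Equal SD:* V = s², so the ratio is p².
- *Others all at the floor, analysing the score itself:* V = p·s² + p(1 − p)·m², where m is the mean distance of the responsive group from the floor. The ratio is p / [1 + (1 − p)(m/s)²].
- *Others all at the floor, analysing change from baseline:* they add neither signal nor noise. If the mean change is small relative to its SD, the ratio is about p.

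| p | Average effect (units of s) | Equal SD | Floor, m = s | Floor, m = 2s | Change score |
|---|---|---|---|---|---|
| 0.9 | 0.45 | 0.81 | 0.82 | 0.64 | 0.90 |
| 0.6 | 0.30 | 0.36 | 0.43 | 0.23 | 0.60 |
| 0.4 | 0.20 | 0.16 | 0.25 | 0.12 | 0.40 |

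For p = 0.6, for example: 0.6² = 0.36; 0.6 / (1 + 0.4 × 1) = 0.43; 0.6 / (1 + 0.4 × 4) = 0.23.

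**Reading.** The direction is the same in every cell. The size is not: at p = 0.6 the retained information runs from 23% to 60% on the variance assumption alone, and at p = 0.9 the average effect hardly moves (0.45 against 0.50).

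**Bias between arms.** Allocation is randomised 1:1, so burn site is balanced in expectation. The dilution affects both arms alike.

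**The case against.** The case for leaving the plan as it is has four parts.

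1. *The floor is inferred from the scale's name.* The protocol lists no DASH items. It says the scale grades symptoms as well as function, and does not say that scoring depends on an upper-limb burn. This stands. A reader might infer that patients without arm burns score at the floor whatever the programme does. The documents support only that they may have little room to change. With burns of at least 10% TBSA, the number with no upper-limb involvement is also unknown.

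2. *A simple squared-share loss cannot be relied on.* It assumes equal SDs, while a group stuck at the floor has almost no spread. This stands too, which is why a range is shown above.

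3. *General function is measured elsewhere.* The BSHS-B physical domain, three EQ-5D-5L dimensions and the pain-interference items of the Brief Pain Inventory are all collected. This stands against the inference that a gain in walking or standing would go unrecorded. It does not answer the mismatch, because none of these is assigned to the physical-functioning objective.

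4. *A DASH subset is ordinary analysis-plan content, and burn site may already be among the clinical characteristics collected.* This is fair for the supportive analysis. It does not reach the main point: the protocol itself fixes an instrument narrower than its objective.

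**Conclusion.** The point holds as a mismatch between one secondary objective and its only assigned instrument. A DASH result describes mainly upper-limb function and should not be reported as general physical role functioning. Some attenuation is probable. Its size cannot be fixed from the documents: it rests on an assumed share of upper-limb burns, an assumed lack of response in the other patients, and an assumed spread of their scores.

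Two further inferences are not supported. The comparison is not biased between arms, since allocation is randomised. Nor does the point weaken the primary outcome or its sample size, which rest on a different scale; no power is claimed for the DASH. The change is worth making because it is cheap and settles how the result will be read. It does not call the trial's main conclusion into question.

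**What to change.** Four changes to the protocol wording:

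1. Under Secondary outcomes, label the DASH as an upper-limb function outcome and word its conclusion that way.
2. For physical role functioning in all randomised participants, prespecify the BSHS-B physical domain together with the EQ-5D-5L mobility, self-care and usual-activities dimensions, all already collected at T0, T1 and T2. The BSHS-B domain should not stand alone: the Primary outcome section itself reports that generic scales are more sensitive than the BSHS-B domains from one month after the burn, and the article does not describe the domain's content.
3. Keep the DASH analysis in all randomised participants.
4. Add a supportive DASH analysis in participants with an upper-limb burn recorded before allocation.

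The cost is wording and at most one baseline field for burn site. No new instrument or visit is needed. There are two small downsides: the general-function measures overlap with the primary quality-of-life instruments, which the report should state, and the supportive DASH analysis rests on fewer participants, with no stratification by burn site described.

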### Participant timeline

All burn survivors at the study site will be screened for eligibility. Enrolment to the study will take place 72 h to discharge from the burn unit. Baseline data collection with a battery of outcome measures along with demographic data. The intervention commences for participants in the treatment group with the pre-discharge component of the programme of care. Weekly follow-ups will be conducted by the nurse case managers. The second phase of data collection will be completed by 8 weeks post-intervention. Follow-up data will be obtained at 4 weeks following the second data collection phase (see Fig. 2).

**Fig. 2 Fig2:**
[figure not shown]
Schedule of enrolment, interventions, and assessments for the nurse-led transitional rehabilitation programme

### Sampling and sample size estimation

Subjects will include adult burn survivors with burn size ≥ 10% TBSA from the Burn Unit. Upon recruitment, randomisation to either control or treatment group (ratio 1:1) with a blinded approach will be carried out. For the pilot phase of the project, the pilot feasibility sample size rule suggested by Whitehead, Julius, Cooper, & Campbell will be used [50]. The rule specifies that a total sample size of 25 participants per arm. Considering possible attrition rate of 20% that has been reported in burn care literature implies that an additional 5 participants will be added to both arms summing up to 30 participants per arm (total = 60 participants).

For the main trial, the sample size calculation based on the primary outcome measure (Burn Specific Health Scale) at 95% confidence level, 90% statistical power and moderate effect size will yield a total of 38 participants per arm [51–53]. Considering an attrition rate of 20%, the final sample size will be 45 participants per arm (total = 90 participants). In all, 150 participants will be recruited for the entire study. For the follow-up process evaluation phase, we will conveniently recruit up to fifteen [15] participants from each arm whilst being guided by the principle of data saturation in addition to the burn care nurses delivering the intervention to complete the qualitative strand. Data saturation will be determined at the point where no new data emerges. The quantitative strand will include review of the recruitment, enrolment, and follow-up records.

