## Trial design

The trial is a double-arm (intervention and control groups), single-centre randomised controlled trial with 1:1 allocation ratio and a follow-up process evaluation phase. We will firstly undertake a pilot feasibility phase and follow-up with the full-scale trial. The null hypothesis is that there will be no difference regarding outcomes between the intervention and control groups. The alternative hypothesis is that there will be statistically significant differences between the participants undergoing the nurse-led programme of care and participants receiving the existing standard of care.

The follow-up process evaluation phase will employ a multi-method approach (qualitative and quantitative strands) to examine the process and issues during the implementation process [34]. Twelve process measures covering domains such as recruitment, follow-up, intervention delivery, and data collection will be considered in the process evaluation phase (see Table 1). The qualitative strand will capture changes in the implementation process and experiences with the intervention from the perspectives of adult burn survivors and nurse case managers. The quantitative strand will offer insight into key process variables such as recruitment, follow-up, and adherence rates. Details regarding the process evaluation phase (process measures, variables, methods, and participants) are provided in Table 1.

**Table 1 Tab1:** Outline of process evaluation for the nurse-led transitional rehabilitation program

Process measures	Process variables	Method	Participants and data collection method
Recruitment and selection rate	• Number of burn survivors screened at the study setting. • Number of participants from the sample of eligible persons. • Number of participants versus aimed number	Enrolment record review	Site manager (research team member)/data collection team
Barriers and facilitators in recruitment and selection process	• Motivation of participating eligible persons. • Experience with recruitment and selection	Semi-structured interviews	Adult burn survivors Recruiting nurses
Follow-up and attrition rate	• Number of participants completing follow-up	Follow-up record review	Site manager (research team member)/data collection team
Barriers and facilitators for follow-up	• Reasons for drop-out • Motivation for continued participation	Semi-structured interviews	Adult burn survivors

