### Statistical methods and analysis

The data analysis plan will proceed through data entry and cleaning, missing data management and statistical analysis. All quantitative data will be coded and entered to SPSS Version 25 (SPSS, an IBM company, Chicago, Illinois, USA). The data will be inspected visually with random searches and frequency counts to ascertain its completeness. Demographic and clinical characteristics will be compared using chi-square test (for normally distributed data) or Mann-Whitney *U* test (data that is not normally distributed). Between group differences will be assessed using independent t test (for continuous data). Both per-protocol (PP) and intention to treat analysis (ITT) will be performed respectively on participants who completed the entire intervention and those recruited to participate. Methods for longitudinal data such as generalised estimating equations (GEE) will be employed. All statistical tests will be conducted at 95% confidence interval.

Qualitative data emerging from the follow-up process evaluation phase will be analysed using content analysis [54]. All audio recordings will be transcribed verbatim and translated from Chinese to English using the Trint Automation Software. The transcripts will be inspected for correctness and completeness by two native speakers who are also fluent in English. The final versions will be exported to the NVivo version 10 software for data management and analysis by two researchers with ongoing consultation with the research team. The analytical process will commence with reading all data repeatedly to achieve immersion and obtain a sense of the whole. Then, data will be read line by line to formulate codes by first highlighting the exact words from the text that appear to capture key thoughts. Following this, the researcher will approach each transcript by making notes of initial impressions. Following the formulation of the codes, labels for the code will be formulated directly from the text. At this point, an initial coding scheme will be formulated. Similar codes will be sorted to formulated categories. Emergent categories will be used to organize and group codes into clusters [54].

Data emerging from the quantitative strand will collated into SPSS Version 25. We will employ descriptive statistics to ascertain the distribution of the data.

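### The 38 per arm does not follow from 90% power and a moderate effect if moderate means d = 0.5 on a two-group comparison; the effect size and method behind it are not stated

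*Protocol article*

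**What the plan says.** Under Sampling and sample size estimation, the main-trial size comes from a "sample size calculation based on the primary outcome measure (Burn Specific Health Scale"), with 95% confidence, and the stated result is that "90% statistical power and moderate effect size will yield a total of 38 participants per arm". A 20% attrition allowance then takes this to 45 per arm, or 90 in total. With a separately sized pilot of 60, the study total is 150. The calculation cites three references. It gives no number or metric for the effect, no SD, no sidedness, no formula and no within-patient correlation.

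Trial design describes a "single-centre randomised controlled trial with 1:1 allocation ratio" and states non-directional hypotheses: "The null hypothesis is that there will be no difference regarding outcomes between the intervention and control groups". Under Statistical methods and analysis, "Between group differences will be assessed using independent t test (for continuous data"). The same paragraph says that longitudinal methods such as GEE will also be used. It does not say which of these is the primary analysis of the Burn Specific Health Scale, or which one the sample size assumes.

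**The concern.** Sample size, power and effect label are given together as one result, so a reader can test whether they fit. On the plainest reading (conventional moderate effect, the named two-group test, two-sided 5%), they do not: the number needed is more than twice the number given.

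The 90% figure is what readers and the ethics board use to judge whether the trial can answer its primary question. If the effect that can be detected at 90% power is about 0.75 rather than 0.5, a non-significant result would say much less about a moderate benefit than the stated power implies.

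**Working it through.** **Inputs.** From the article: alpha 0.05, power 90%, 1:1 allocation, 38 analysed per arm, 45 recruited per arm, 20% attrition, independent t test. Two-sided testing is read from the non-directional hypotheses. Assumption: moderate means d = 0.5. The article gives no number, so a range is shown below.

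**Reproducing the stated figure.** The normal approximation is n per arm = 2(z₀.₉₇₅ + z₀.₉₀)²/d², and 2(1.960 + 1.282)² = 21.01.

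- d = 0.5: 21.01/0.25 = 84.06, so 85 per arm. The noncentral t gives 85.03, so 86.
- d = 0.75: 21.01/0.5625 = 37.36, so 38 per arm. This returns the stated number, but at 0.75.

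Other settings at d = 0.5 do not return 38. One-sided with 90% power needs 70, two-sided with 80% needs 64, and one-sided with 80% needs about 50.

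**Power with 38 per arm.** At d = 0.5 the noncentrality is 0.5 × √(38/2) = 2.179. The normal approximation is Φ(2.179 − 1.960) = 58.7%, and the noncentral t gives 57.6%. Over a range of effects (t test, two-sided 5%):

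| Assumed d | Power, 38 per arm |
|---|---|
| 0.4 | 41% |
| 0.5 | 58% |
| 0.6 | 73% |
| 0.7 | 85% |
| 0.75 | 90% |
| 0.8 | 93% |

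The difference detectable with 90% power is 0.753. After 20% loss from 45, 45 × 0.80 = 36 per arm remain. Power at d = 0.5 is then 55%, and the detectable difference is 0.775.

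**Pooling pilot and main trial.** 150/2 = 75 per arm gives 86% at d = 0.5. After 20% loss, 75 × 0.80 = 60 per arm gives 78%.

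**Baseline-adjusted analyses at d = 0.5.**

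- Single visit: the required n is multiplied by (1 − ρ²). At ρ = 0.75, 86 × (1 − 0.5625) = 37.6.
- Mean of T1 and T2, with one common correlation ρ among the three visits: the multiplier is (1 + ρ)/2 − ρ². At ρ = 0.6 this is 0.80 − 0.36 = 0.44, and 86 × 0.44 = 37.8. At ρ = 0.5 it is 0.75 − 0.25 = 0.50, and 86 × 0.50 = 43.

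**Repeated-measures ANOVA at f = 0.25, three visits, correlation 0.5, 90% power.** The between-group effect needs 58 per arm and the group-by-time interaction needs 18. Neither is 38.

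**The case against.** The strongest reply is that the article never commits to d = 0.5. It says "moderate effect size will yield a total of 38 participants per arm" and gives no number. The standard formula at 0.75 returns exactly 38, and 0.75 is still below the conventional large value of 0.8. If the authors called a value between 0.5 and 0.8 moderate, the fault is an unquantified label and not a miscalculation. This stands as far as it goes: the 58% is conditional. A reader of the published claim would still not expect moderate to mean 0.75, and power at 38 per arm falls short of 90% at every tabulated effect from 0.4 to 0.7.

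Second, the t-test sentence follows the comparison of demographic and clinical characteristics and is not tied to the primary outcome, while GEE is planned and the outcome is measured three times. A baseline-adjusted analysis at a correlation near 0.6 would make about 38 per arm adequate at d = 0.5, and an interaction test at f = 0.25 could need far fewer. That is plausible, but the article does not link the sample size to any such analysis or state a correlation.

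Third, 150 will be randomised, and power is better if all are analysed together. The article sizes the 90 separately and does not say that pilot data will be pooled. Pooling would not restore 90% at d = 0.5 in any case.

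Fourth, the cited references or the full protocol may hold the missing inputs. They may. The point is not that detail is absent, but that the published figures do not fit together under the test the article names.

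**Conclusion.** The point holds in conditional form. If moderate means d = 0.5 and the comparison is an unadjusted two-sided t test at 5%, the stated 38 per arm should be 86, and the power it gives is about 58% (55% at 36 per arm), not 90%. The stated power is met only for a difference of about 0.75. Full pooling of the 150 narrows the gap to 86% or 78% without closing it.

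A reader might infer more: that the trial is certainly underpowered, with little better than even odds of detecting its target effect, or that the authors made an outright arithmetic error. The documents do not support either reading. The value 0.5 is an assumption, the planned longitudinal analysis could be considerably more efficient, and 38 is what the usual formula gives at 0.75. What is established is that the stated power, effect label and number do not agree on the plainest reading, and that the article states nothing that reconciles them.

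**What to change.** Rewrite the main-trial paragraph under Sampling and sample size estimation in one of two ways:

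1. If the basis was a two-group comparison, state that 38 analysed per arm gives 90% power for a standardised difference of about 0.75 and about 58% for 0.5 (two-sided 5%, t test), and drop the word moderate.
2. If the basis was a baseline-adjusted or GEE analysis, state the numeric effect size, the sidedness and the assumed correlation, and name that analysis as primary for the Burn Specific Health Scale under Statistical methods and analysis.

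The cost is one paragraph, plus one sentence in the analysis section under option 2. No extra patients are needed to correct the claim. Under option 1 the stated power or target effect becomes less favourable.

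### The 20% attrition allowance is miscalculated: 45 per arm leaves 36 evaluable, not the 38 required, and the pilot repeats the error

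*Protocol article*

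**What the plan says.** The point sits in the protocol article, section Sampling and sample size estimation, which sizes two phases one after the other.

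- **Pilot.** The base number comes from a published rule of thumb: "The rule specifies that a total sample size of 25 participants per arm". The allowance for loss is introduced with "Considering possible attrition rate of 20% that has been reported in burn care literature", and the operation is spelled out: "an additional 5 participants will be added to both arms summing up to 30 participants per arm (total = 60 participants").
- **Main trial.** The calculation is described as "at 95% confidence level, 90% statistical power and moderate effect size", and the result is that a "moderate effect size will yield a total of 38 participants per arm". The allowance follows: "Considering an attrition rate of 20%, the final sample size will be 45 participants per arm (total = 90 participants").

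The two totals, 60 and 90, are added to give 150 for the whole study. The abstract repeats that figure.

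**The concern.** An attrition allowance exists so that the required number is still present after the expected loss. That means dividing the required number by the proportion retained. Adding the attrition percentage to the required number always gives too few, because the loss then applies to the larger, inflated figure.

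The pilot text shows the additive method openly, since 5 is 20% of 25. The main-trial figure fits the same method followed by rounding down. If so, each phase falls below its own target at exactly the attrition rate it was meant to absorb. The 90% power claimed for the main trial would not be met on the plan's own assumptions. Attrition is not a remote risk here: the Discussion names dropout as the anticipated limitation of the study.

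**Working it through.** **Inputs**, all from Sampling and sample size estimation: main trial 38 per arm required, 20% attrition, 45 per arm stated; pilot 25 per arm required, 20% attrition, 30 per arm stated; total 150.

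**Step 1. Reproduce the plan's figures.** Adding 20%, n × (1 + 0.20):

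- Pilot: 25 × 1.20 = 30, exactly as stated.
- Main trial: 38 × 1.20 = 45.6. Rounding down gives the stated 45; the usual rounding up would give 46.

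The protocol does not show the operation for the main trial, so this is the method consistent with 45, not one it declares.

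**Step 2. Apply the allowance correctly.** n / (1 − 0.20), rounded up:

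- Main trial: 38 / 0.80 = 47.5, so 48 per arm (96 in total).
- Pilot: 25 / 0.80 = 31.25, so 32 per arm (64 in total).
- Both phases: 96 + 64 = 160, against 150 stated.

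**Step 3. What the stated sizes deliver at 20% loss.**

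| Phase | Recruited per arm | Left after 20% loss | Required | Shortfall per arm | Shortfall in total | Largest loss covered |
|---|---|---|---|---|---|---|
| Main trial | 45 | 45 × 0.80 = 36 | 38 | 2 | 76 − 72 = 4 | 1 − 38/45 = 15.6% |
| Pilot | 30 | 30 × 0.80 = 24 | 25 | 1 | 50 − 48 = 2 | 1 − 25/30 = 16.7% |

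Rounding 45.6 up instead of down would not have cured it: 46 × 0.80 = 36.8, still below 38.

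**Step 4. Cost in power, main trial.** The protocol gives only "90% statistical power and moderate effect size", with no numerical effect and no standard deviation. I therefore solved for the standardised difference d at which 38 per arm gives 90% power in a two-sample t test at alpha 0.05, then evaluated power at 36 per arm with the same d:

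- Two-sided: d about 0.75; power at 36 per arm about 88.4%.
- One-sided (sidedness is not stated): d about 0.68; power at 36 per arm about 88.5%.

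Normal-approximation check, two-sided: d = (1.960 + 1.282) × √(2/38) = 0.744; power = Φ(0.744 × √(36/2) − 1.960) = Φ(1.195), about 88.4%.

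The loss is about 1.6 percentage points two-sided. The pilot has no power target, so no such figure applies to it.

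**The case against.** Four points can be made on the other side.

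1. **The effect is small.** This stands. Two participants per arm and about 1.6 points of power do not undo the design. In the pilot, ending at 24 instead of 25 against a rule of thumb defeats no inferential aim. This limits the weight of the point but does not make the figures right.

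2. **The phases may be pooled.** The abstract speaks of block randomising 150, and the section on sequence generation describes a list of 75 sets. If both phases enter one analysis, 75 × 0.80 = 60 per arm remain and the main-trial shortfall disappears. But Trial design places a pilot feasibility phase before the full-scale trial, the sample size section sizes each phase separately, and nowhere does the article say that the data are combined. The shortfall applies if the main trial is analysed alone, which is how it is sized.

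3. **Dropouts may still contribute data.** Statistical methods and analysis plans an intention-to-treat analysis and generalised estimating equations. Eligibility criteria counts any exit before week 12 as dropout, so someone lost between week 8 and week 12 can still supply week 8 data. Thus 36 is the expected number of completers, and some analyses may use more. This is fair, but the plan itself chose to inflate 38 for 20% loss, and nothing in the analysis section withdraws that allowance. The per-protocol analysis is restricted to completers in any case.

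4. **Adding 20% is a common convention.** It is common, but it does not do what the text says it does. In the main trial, 45 is below even what that convention gives when rounded up (46).

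**Conclusion.** The figures are wrong as written. At the stated 20% attrition, 45 per arm yields 36 against the 38 required, and the pilot's 30 per arm yields 24 against 25. The sizes cover 15.6% and 16.7% loss. These results use only the protocol's own numbers.

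The consequence is modest: power of about 88.4% where 90% is claimed. That figure assumes a two-sided 5% test and the effect of about 0.75 implied by 38 per arm, and that the main trial is analysed without the pilot data. The pilot discrepancy is the same slip with little practical consequence. The point merits correction because a stated number contradicts its stated inputs, not because the trial is materially compromised by it.

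**What to change.** Keep the recruitment figures and correct the statement, in one of two ways:

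- State that at 20% attrition 36 per arm (main trial) and 24 per arm (pilot) are expected to be evaluable, and quote main-trial power on 36. This requires writing down the numerical effect size and the sidedness of the test, which the section does not now give.
- Or state that 45 and 30 per arm preserve the targets of 38 and 25 up to attrition of 15.6% and 16.7%.

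If the pilot data are meant to enter the main analysis, say so and give the power for that analysis.

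The cost of any of these is wording only. If the sponsor prefers to hold both 38 and 20%, the matching recruitment figure is 48 per arm. That is a larger change: the total rises above 150, the list of 75 sets would need extending, and the ethics board and registry would have to be told, as the Ethics and dissemination section requires for modifications. For a gap of this size, that is not needed to put the document right.
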